## Material and design

### Summary of aims

The objective of the SNEACY study is to test several aims: (1) Investigate basic laboratory and applied scholastic performance aspects of brain function, cognition, and academic achievement following aerobic exercise compared to active (i.e., Trier Social Stress Test for Children (TSST); a commonly used psychosocial stressor) and passive (i.e., seated rest) control conditions; and (2) Investigate phasic changes in SNS activation (as indicated by sAA) as a potential mechanism for the transient beneficial effect of exercise on brain function, cognition, and academic achievement. Phasic activation refers to brief, rapid changes in the SNS [17] in response to salient or task-relevant information in the stimulus environment [18]. Phasic sAA has been shown to be related with attention, memory, and various academic outcomes [16, 18–22]. SNEACY is a randomized crossover trial with three acute interventions: 20 min of moderate intensity treadmill exercise, 20 min of seated rest, and a 14-min TSST for Children. The TSST and seated rest interventions serve as active and passive control conditions, respectively, for the experimental intervention involving moderate intensity exercise. As a result of this design, changes observed in the aerobic exercise intervention can be attributed to the exercise component of the intervention rather than to other, potentially confounding factors, such as expectancy effects, stress, or elevated heart rate. The study will enroll and randomize 103 typically developing, 9–10-year-old children. We hypothesize that exercise-induced phasic increases in SNS activity, indicated by sAA levels, will mediate the effect of a single bout of exercise on brain function (i.e., P3 amplitude and latency), cognition (i.e., executive control), and standardized achievement test performance (i.e., mathematics, reading). To further explore a relation between exercise-induced change in sAA with brain and cognition, baseline and stress-induced (i.e., exercise, TSST) change in cortisol will be investigated as a potential factor in the analytical model. All participants provide written assent/consent (and legal guardians provide written informed consent) by a trained research technician in accordance with the Institutional Review Board of Northeastern University. The study was designed in accordance with the SPIRIT statement, details are provided in Fig. 1.

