### Power and analytic strategy

A traditional power analysis was conducted to estimate the appropriate sample size necessary for detecting a mediating effect of sAA levels on the relationship between a single bout of aerobic exercise and acute changes in cognition given the inclusion of potentially confounding variables (e.g., age, sex, BMI, IQ, SES) based on a one-sided alpha of .01 to correct for multiple outcomes and a power of 0.8. For the total effect of exercise on the ERP and cognitive outcomes, an effect size was calculated from the results reported in Hillman et al. [9], which observed increased P3 amplitude, task performance, and scholastic achievement following acute exercise relative to rest in a sample of preadolescent children resulting in a moderate-to-large effect size (Cohen’s *d* = 0.79). Therefore, assuming a medium size of Cohen’s *f*2 = 0.15 for the total effect and 8 predictors (including exercise condition, subject ID, and covariates) in the regression model, power analysis indicate that a sample size of 82 participants will provide adequate power to detect the effects of a single bout of exercise on neuroelectric function and behavioral performance. For the mediation analysis, medium effect sizes [33] were assumed for both the direct effect of exercise on sAA levels (path a: coefficient = a) and the direct effect of sAA level on the outcomes controlling for treatment condition (path b: coefficient = b). Corresponding to Cohen’s [34] criteria for medium (13% of the variance) effect size, the values of a and b were set at 0.39. Applying the Sobel [35] first-order test, the indirect effect or the mediated effect of exercise on outcomes through sAA was indicated by the product of a and b and was tested. Empirical power results [36] showed that a sample size of *N* = 103 per study was required to detect the presence of mediation. Accordingly, we aim to recruit *N* = 120 to account for attrition.

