We will investigate whether the effect of the experimental conditions (*x*) on brain function, cognition, or academic achievement (distal *y* outcomes) is mediated by sAA and CORT baseline levels (*i*) and sAA change (*s*) using a path modeling framework (Mplus v8) and conventional model-to-data fit indices [37]. Each model will be adjusted for the set of potentially confounding variables (e.g., age, sex, BMI, IQ, SES). We will interpret significant direct effects on each outcome as supporting our hypotheses. We aim to incorporate the change process of sAA (*s*) and CORT (*s*) within the same model (allowing s and s to covary). We will utilize the most current and recommended practices [38, 39] for testing moderated mediation framework that leverages the stability of the entire sample for model estimation (causal structure); 5000 bootstrap draws will be run to collect the bias-corrected bootstrapped confidence intervals (95% CI) and significant indirect effects will be decomposed in Mplus output (identical to the Sobel test [35]). If mediation is found, subsequent tests of moderation will be conducted. To test the effect of the treatment condition (i.e., exercise, TSST-C, rest) on univariate continuous outcomes (brain function, cognition, academic achievement), three separate models will be tested using planned comparisons with imposed group invariance constraints. Group comparisons in sAA mean can be simultaneously compared (Is sAA larger in exercise compared to TSST-C and/or rest?), while also comparing benefits in the continuous outcomes regressed on sAA.

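### The analysis text does not keep the Aim 1 condition contrast separate from post-condition sAA, so the total effect of exercise could be replaced by an sAA-adjusted direct effect

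*Protocol article*

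**What the plan says.** All references are to the protocol article.

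- **Aim 1** (*Summary of aims*) is to study "brain function, cognition, and academic achievement following aerobic exercise compared to active" (TSST) and passive (rest) controls. *Primary outcome* names changes in cognitive performance after each of the three interventions. Both are contrasts between conditions.
- **Power** (*Power and analytic strategy*, first paragraph) treats this effect on its own, beginning "For the total effect of exercise on the ERP and cognitive outcomes". It assumes f² = "0.15 for the total effect and 8 predictors (including exercise condition, subject ID, and covariates) in the regression model" and concludes that "a sample size of 82 participants will provide adequate power to detect the effects of a single bout of exercise". The covariates given as examples are age, sex, BMI, IQ and SES. sAA enters only afterwards, in the mediation calculation, which gives N = 103 (120 with attrition).
- **Analysis** (same section, second paragraph) starts with a path model for mediation. It says that significant direct effects on the outcomes will count as support for the hypotheses and that significant indirect effects will be decomposed. It then turns to the conditions: "To test the effect of the treatment condition (i.e., exercise, TSST-C, rest) on univariate continuous outcomes", three models with planned comparisons under invariance constraints across groups are to be fitted. The closing sentence says that sAA means can be compared at the same time, "while also comparing benefits in the continuous outcomes regressed on sAA".

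**The concern.** sAA is sampled after each intervention, is expected to rise with exercise, and is the proposed mechanism. Regressing the outcome on it and then comparing conditions answers a different question from Aim 1: what exercise does apart from its effect on sAA. The better the sAA hypothesis holds, the smaller that answer becomes. In the limit of full mediation it is zero although exercise works, and the test rejects only at its alpha.

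A second cost is that randomised order protects the plain condition contrast but not one conditioned on a variable that the condition changes. Unmeasured factors that move both sAA and cognition on the day can then bias the comparison.

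**Working it through.** **1. Which effect each place names**

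| Place | Effect named | sAA in the model? |
|---|---|---|
| *Summary of aims*, Aim 1 | outcomes by condition (total) | not mentioned |
| *Power and analytic strategy*, first paragraph, N = 82 | total effect | not named among the predictors |
| Same section, second paragraph, path model | direct and indirect | yes |
| Same paragraph, sentence announcing the planned comparisons | effect of condition | not mentioned |
| Same paragraph, closing sentence | outcome benefits | yes, outcomes regressed on sAA |

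The analysis paragraph names direct and indirect effects but not their sum. Its only account of how benefits are compared has sAA as a regressor.

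**2. The plan's own figure**

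Inputs: f² = 0.15, 8 predictors, and "based on a one-sided alpha of .01 to correct for multiple outcomes and a power of 0.8". For one regression coefficient, use a noncentral t with ncp = √(f²·N) and df = N − 8 − 1.

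- Two-sided .01: N = 82, power 0.803. The stated 82 is reproduced.
- One-sided .01, as stated: N = 70. Power is 0.868 at N = 82 and 0.94 at N = 103.

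So 82 is a size for a total effect with no sAA term. The mismatch in sidedness is a separate matter.

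**3. What adjustment for sAA would remove (exercise versus rest)**

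Inputs: "the values of a and b were set at 0.39" and total f² = 0.15. My assumptions are condition scaled to unit variance (±1 coding), residual variance 1 for sAA and for the outcome given sAA, and independent observations.

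- Indirect effect: ab = 0.39 × 0.39 = 0.152.
- Total coefficient c: √0.15 = 0.387, or √(0.15 × (1 + 0.39²)) = √(0.15 × 1.152) = 0.416 when the mediator's share of the residual variance is counted.
- Direct coefficient c′ = c − ab: 0.387 − 0.152 = 0.235, or 0.416 − 0.152 = 0.264.
- Share removed: 0.152/0.387 = 39%, or 0.152/0.416 = 37%.

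**4. Power at N = 103, one-sided .01 (critical value 2.326), normal approximation**

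- SE(c) = √((1 + b²)/103) = √(1.152/103) = 0.106. SE(c′) = √((1 + a²)/103), also 0.106.
- Total effect: 0.387/0.106 gives power 0.91, and 0.416/0.106 gives 0.95.
- Adjusted effect: 0.235/0.106 gives power 0.46, and 0.264/0.106 gives 0.57.

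The lower end of each range takes c as if the total residual variance were 1 but uses 1.152 in the standard error, so it is pessimistic. The upper end is internally consistent.

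**5. Cross-check with the noncentral t**

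Direct f² = 0.264²/1.152 = 0.060, with 9 predictors and one-sided .01. Power is 0.44 at N = 82, 0.55 at 103 and 0.63 at 120, and 80% power needs N = 170. The like-for-like figures for the total effect are 0.94 at N = 103 and N = 70 for 80% power.

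**The case against.** The strongest reply is that the plan never says the Aim 1 contrast is adjusted for sAA. Five points support it.

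- The sentence that defines the condition test contains no sAA. The closing sentence is permissive and additive in tone, and can describe a further comparison. **This stands.** A reader might infer that Aim 1 is certainly tested on sAA-adjusted outcomes, and the text does not establish that.
- A reader might also infer that the plan contains no model without sAA. **The documents contradict that.** The regression behind N = 82 names condition, subject ID and covariates only. It appears in the sample-size argument, however, and the analysis paragraph does not carry it forward as the Aim 1 analysis.
- With invariance constraints, the closing words may mean comparing outcome-on-sAA slopes across conditions, and a path model can return the total effect as direct plus indirect. **Both are possible.** But a slope comparison is not the total effect either, and the paragraph never says that the sum will be estimated or tested.
- The statement that direct effects support the hypotheses is weak evidence, because the power paragraph uses the same term for exercise on sAA and for sAA on the outcomes. **This stands**, and the point does not rest on that statement.
- A journal article condenses, and model detail may sit in an analysis plan. **This stands in part.** The point is not absent detail. The article does describe an outcome comparison, and that description does not match its own aim and power model.

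**Conclusion.** The point holds as an unresolved estimand. The aim and the power calculation call for a total effect, while the analysis paragraph describes the outcome comparison with a post-condition mediator as regressor and names only direct and indirect effects. Followed literally, it yields an sAA-adjusted contrast or a comparison of slopes.

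If the adjusted contrast were used for exercise versus rest, the effect would fall by about 37–39% and power at N = 103 from about 0.91–0.95 to 0.46–0.57. These figures join two separate planning assumptions (total f² = 0.15; a = b = 0.39) in one between-person model with unit residual variances. They show that the choice matters. They are not a power calculation for the crossover.

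Two stronger inferences are not supported:

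- **That the trial was sized on the total effect.** The total effect gave N = 82. The governing N = 103 comes from the mediation test.
- **That the loss applies to every Aim 1 contrast.** The *Discussion* expects sAA to rise after both exercise and the TSST, so for that pair path a, and with it the loss, may be much smaller.

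**What to change.** In the second paragraph of *Power and analytic strategy*:

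1. State that Aim 1 is tested by planned contrasts of exercise with rest and with the TSST, in a model with condition, design terms and pre-condition covariates only. Post-condition sAA and cortisol stay out, in line with the total-effect model in the power paragraph.
2. State that the sAA-adjusted condition effect is reported only under Aim 2, as the direct effect beside the indirect effect.
3. Reword the closing sentence so that the outcome-on-sAA regression clearly belongs to Aim 2.

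The cost is a few sentences and one simpler model per outcome. No change to data collection or sample size is needed.

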### Dissemination plan

Upon completion of the study, we aim to disseminate and publicize the results to school administrators, policy makers, research study participants, and the general public by utilizing diverse strategies. Widespread dissemination will occur following study completion and publication, with the main results as well as secondary and ancillary results by employing the following techniques: (a) media coverage through press releases and interviews targeted to local and national news outlets; (b) production of a research summary document and “facts sheet” targeted to the general public, which summarizes key study conclusions; (c) production of flyers, posters, brochures, and research briefs targeted to broad audiences; (d) study newsletters targeted to study participants; (e) distribution of dissemination materials to community agencies, professional societies and health-related websites and list-serves; and (f) mailing personal thank you letters that include the main findings to research study participants.

## Discussion

The SNEACY study is a large, ongoing randomized crossover trial with a goal of investigating phasic changes in SNS activation (indicated by differential sAA and CORT trajectories) as a potential mechanism for the transient beneficial effect of moderate intensity exercise on brain function, cognition, and academic achievement in cognitively normal children. We predict that following the cessation of moderate intensity exercise performance on executive function tasks will improve, with enhanced neuroelectric functioning and that these improvements will be linked to changes in sAA. In addition, both sAA and cortisol are expected to increase in response to both exercise and the TSST-C in children. This is a well-designed and controlled study, with the exercise prescription individualized to each child reflecting their specific moderate intensity exercise. We further predict that academic performance will be greatest following exercise.

While this is a well-designed, detailed study, it is not without its limitations. The findings from this study will not allow us to determine whether different doses of exercise (i.e., duration, intensity, etc.) result in differences is neuroelectric profiles and cognition. However, we do expect to observe differences in performance based on an individual’s fitness and body composition. Our active control intervention is designed to increase psychosocial stress for the participants, and to increase their heart rate as a result. However, our passive control group is seated at quiet rest and prior research does not indicate cognitive benefits following seated rest [8–10]. In this sense, this is a well-controlled study with the inclusion of positive (TSST-C) and negative (seated rest) conditions. Finally, it would be impossible to measure all individual differences across our participants, which could influence their performance following interventions. There are several challenges that large-scale studies such as this one face. Primarily, ensuring accurate saliva measures from children may be a challenge, and relies on day of pre-intervention compliance from children and their parents. In addition, children must produce enough saliva in a set amount of time. Maintaining compliance and interest over a number of visits for children may be challenging as well.

Taken together, the SNEACY study will be among the first to investigate the molecular underpinnings of the acute exercise-induced changes in cognition and brain in children through a combination of molecular, neuroimaging, behavioral, and academic achievement measures. Previous data indicates that a single bout of aerobic exercise increases sAA [15, 40, 41] and salivary CORT [42–45], reflecting increased activation of the SNS and glucocorticoid system following an exercise bout, respectively. Acute exercise has also been related to enhanced cognition [20] and acute elevations in sAA and CORT [42, 46]. For example, in a study with older adults, memory was enhanced after a brief exercise bout, and changes in sAA following exercise correlated with improvements in memory [20]. However, data from the present study will aid in our understanding of the relationship between exercise, cognition, and the SNS and adrenal systems.

Therefore, we will examine changes in behavioral and brain measures following a single, brief bout of exercise, and seek to explain these shifts through phasic changes in sAA that are reflective of SNS activity. Through the collection of salivary, neuroimaging, and behavioral outcomes in the proposed randomized crossover experiment, we can begin to establish the multidimensional nature of the transient effects of a single bout of exercise on the underlying molecular and neural changes that promote cognitive health and academic achievement during preadolescent childhood.

## Data Availability

Not applicable. Data collection is ongoing. When complete, the datasets will be available from the corresponding author on reasonable request.

## Abbreviations

ADHD: Attention deficit hyperactivity disorder
BMI: Body mass index
CRF: Cardiorespiratory fitness
CORT: Cortisol
DXA: Dual-energy X-ray absorptiometry
EEG: Electroencephalogram
ERPs: Event-related brain potentials
HR: Heart rate
IEP: Individualized education plan
IQ: Intelligence quotient
ISI: Inter-stimulus interval
MVPA: Moderate-to-vigorous physical activity
PA: Physical activity
sAA: Salivary alpha-amylase
SNEACY: Sympathetic Nervous System & Exercise Affects Cognition in Youth
SES: Socio-economic status
SNS: Sympathetic nervous system
TSST: Trier Social Stress Test
RPE: Ratings of perceived exertion
